### Intervention

Before the start of the intervention visits, the PLWH in both the intervention and control arms receive similar preparatory visits.

#### Preparatory visits (month 1)

In the first preparatory visit, the study is introduced by the CHW and consent is asked to collect information about the PLWH and the contact details of the household members. Furthermore, in this first visit an assessment is made of the PLWH’s ART adherence (by doing a pill count) and household context (by doing a home assessment).

Between the first and second preparatory visit, a household member will be randomly selected from the information sheet collected by the CHW at the first visit and be contacted for a household interview. If the research team was not able to contact or interview the first randomly selected household member, then a second or third household member will be contacted. The interview with the household member must occur before the first intervention visit. If the research team fails to interview a household member within this time frame, no household member interview will be conducted related to that patient.

In a second preparatory visit, which is a standard of care visit that all patients enrolled in the study receive, an evaluation of the ART adherence (pill count) will be repeated. A fieldworker will accompany the CHW during this visit, and conduct and conduct afterwards a baseline interviews.

#### Intervention visits (months 2–8)

After completion of these initial preparatory visits, the intervention will start. In the control arm, the CHW will offer a standard package of support (i.e. a pill count) focused at the individual level. In the intervention arm, in addition to the pill count the CHW activities entail two additional components: 1) an additional individual-level component to stimulate the self-management skills of the HIV patient; and 2) a context-focused component for promoting HIV competent households.

Figure 1 outlines an overview of the intervention visits. Intervention visits are instructive, sessional and deliberately structured to systematically deliver the intended content of the intervention. In between these main visits, time has been provided for catch-up visits in case a CHW could not finish a previous main visit. In the first two main visits (hereafter called visits) focus is placed on the individual level development. The third and fourth visits focus at the interpersonal level by examining healthy communication and disclosure. The fifth and sixth visits are household-level focused, aiming to stimulate HIV competency in the household. The seventh session completes this intervention by revisiting the previous sessions and developing a long-term household support plan.

**Fig. 1 Fig1:**
[figure not shown]
Intervention visits related to the Positive Communication Process (P²CP). ART antiretroviral treatment, HIV human immunodeficiency virus, P2CP positive communication process, PLWH person living with HIV

Because disclosure is a critical component within HIV competent households and a common thread throughout delivery of the intervention, at the end of each and every intervention visit the PLWH will be encouraged to invite and, where possible, bring a household member or sexual partner to the next visit. If a new household member or sexual partner joins a session, their knowledge about HIV and ART will be assessed and improved by means of a visual HIV fact sheet. The household member/sexual partner will be included in the activities for the remainder of the intervention visit and be invited to join the next visits as well. If the PLWH did not bring a sexual partner or household member to the visit, the CHW will invite the PLWH to do so at the next visit. However, while highly encouraged to bring a household member, this is not a prerequisite to continue the intervention.

#### Piloting the HIV competent household intervention

The intervention pilot was undertaken with a small subsample of two ART patients in the intervention community from a facility not included in the RCT. The outcomes were incorporated into the final intervention. The feedback from the pilot included the need to allow for the possibility for “in between visits” to catch up on any activities that were not completed during the previous session. The pilot also demonstrated the need for more time than had been planned for CHW training. More engagement with the CHWs was therefore included in the training, with more role playing and simulated intervention time rather than time allocated for them to read the manual and self-learn.

#### Implementation of the HIV competent household intervention

The CHWs who are part of the intervention arm received 9 training days with a focus on role play and ensuring that the CHWs understand the intervention and the importance of standardisation of the delivery. At the end of the training, the CHWs were informally assessed to evaluate the grasp of content and technique to deliver the intervention. Furthermore, regular debriefing sessions are planned with the CHWs to monitor compliance with the intended standard of the intervention delivery and to improve adherence to the intervention protocols.

Various strategies are followed to maximise participant retention in the study. First, potential participants who return for follow-up care and treatment visits after the initial diagnosis visit are recruited into the study. Patients who return for follow-up treatment and care portray commitment to their own health betterment and are as such perceived as patients who are likely to commit to long-term participation in the Sinako study. Second, CHWs have been trained to answer pertinent questions about the study that may be posed by potential participants at every opportunity or as and when requested. Third, tailored strategies are used specific to the individual participant. For instance, a potential participant of the Sinako study will, from time to time, travel out of the province. This poses a risk of attrition from the study. To mitigate this risk and improve retention rates, the CHWs have been trained to check with the enrolled patients regarding travelling plans. In addition, the patient is also requested to inform the CHW of such travel, whether planned or occurring as an emergency. Finally, the CHW follow-up visits with the patient or the fieldworker data collection appointment with the household member are, as far as possible, scheduled according to the participants’ convenience. This is to ensure that study activities adapt to participants’ availability and are not imposed. This in turn is intended to improve retention.

If an individual participant does not want to continue participating in the study the intervention for this particular respondent will be stopped. In case of a particular adverse event (e.g. admission to a hospital), the principal investigator will make an informed decision whether or not to continue the trial for this particular participant.

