## Methods/design

### Trial design

The primary activity for the Sinako study will be the implementation and assessment of the impact of an HIV competent household intervention. Table 1 represents a schedule of intervention implementation, assessment and dissemination. The intervention will be assessed in a cluster-randomised control trial (RCT) with two arms. CHWs will be the primary actors in this RCT, either continuing to deliver a standard ART adherence support service (arm 1), or a standard ART adherence support service plus a household P^2^CP intervention (arm 2). CHWs, however, are linked to a health care facility, which creates a risk of contamination when CHWs active in different arms operate from the same facility. The facility was therefore selected as the cluster unit of randomisation. The health care facilities in the study setting were categorised as large or small facilities according to the numbers of CHWs employed, which also corresponds to the number of patients. Subsequently, 12 facilities were grouped by selected subdistricts and were randomly selected from the list of facilities for inclusion in the study in arms 1 and – resulting in six facilities or clusters per trial arm. Further blinding of the study arms was not possible because of the clear differences between the intervention and the standard of care. The design and report of this clinical trial protocol follows the Standard Protocol Items: Recommendations for Interventional Trials (SPIRIT) statement (Additional file 1).

**Table 1 Tab1:** Schedule of intervention implementation, assessment and dissemination

	Year 1	Year 2	Year 3	Year 4
Preparatory research activities				
Ethical approval	X			
Preparatory literature review	X			
Quantitative survey development	X			
Mobile data collection tool programming	X			
Qualitative questionnaire development		X		
Development of the household intervention	X	X		
Pilot of the household intervention		X		
Drawing study sample for cluster-RCT		X		
Fieldworker training		X		
Baseline assessment of HIV competence and HIV outcomes				
Baseline quantitative data gathering, capturing and cleaning		X		
Qualitative data collection		X	X	
Baseline quantitative data analysis			X	X
Writing of reports and articles		X	X	X
Implementing the household intervention				
Workshops providing training to CHWs conducting the intervention		X		
Screen participants for eligibility		X		
Informed consent		X		

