### Outcomes

In order to assess the impact of the intervention, key baseline assessment indicators are considered. These include primary and secondary outcomes (Table 2). As the current study aims to optimise the impact of CHW support on individual ART outcomes by stimulating HIV competent households, the primary outcomes for this study are: 1) patient’s viral load and 2) ART adherence (measured by the Adherence to Combination Therapy Questionnaire [31]). Data on ART adherence is collected from the enrolled individual by the research team. In addition, departmental permission has been requested to access the viral load data already collected by the Department of Health. As such, this study only requires secondary access; viral loads will not be collected by the research team.

**Table 2 Tab2:** Outcomes for pre- and postintervention assessment

Primary outcomes	
• Viral load	
• Adherence to antiretroviral treatment	
Secondary outcomes	
Individual-level:	
• HIV knowledge	
• Condom use	
• Quality of life	
• Self-management	
• Disclosure	
• Perceived social support	
Household/-level:	
• HIV knowledge	
• Condom use	
• HIV-related stigma	
• Communication about HIV	
• Household functioning	
• HIV testing	
• Support to a household member living with HIV	

*HIV* human immunodeficiency virus

Moreover, we assess the impact of our intervention on a range of secondary process-related outcomes, measuring both individual outcomes and aspects of HIV competence of the households, which should facilitate individual ART adherence (and thus support the primary outcomes). At the individual level, the PLWH questionnaire assesses HIV knowledge, condom use, quality of life, self-management, perceived social support and disclosure. Outcomes measured at the household level include HIV knowledge, condom use, HIV-related stigma, communication about HIV, household functioning, HIV testing and support to a household member living with HIV. These outcomes are included as indications of household comfort with HIV and communicating about HIV and could be considered as proxy measures for HIV competency at the household level.

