##### Follow-up data collection

In order to ensure maximum comparability, the postintervention questionnaire collects information on the same outcomes as the baseline questionnaire from the same respondents in both the intervention and control arms of the RCT. The same data gathering procedure will be followed for the post-intervention assessment as for the baseline data collection. If a patient drops out, the research team will try to trace the patient to understand the reason for this loss to follow-up.

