### Data analyses

#### Quantitative data analysis

The comparison between the two arms using cluster-specific analysis techniques will allow us to assess the net impact of the household intervention on both the primary and secondary outcomes. First, we will perform an intent-to-treat analysis. In a second step, an analysis based on dose-response data will be conducted.

Furthermore, the main relationships between the relevant concepts (household intervention, HIV competence, prevention and treatment outcomes) will be analysed using latent cross-lagged modelling (Mplus). Using chi-square difference testing [36], measurement invariance will be tested to assess whether the latent factors are fully scalar invariant over time (pre- and postintervention). The latent factors will be modelled accordingly in the structural models over time [37]. The analyses will control for demographic and social characteristics, and the medical and medication history of the patient. Furthermore, other quantitative data analysis methods will be used to analyse the baseline and follow-up quantitative data, such as latent cross-lagged modelling, multilevel modelling, logistic regression and Poisson regression, among others. In this way, these results will allow us to successfully reach our research aims, namely to develop and scientifically test the impact of a household intervention on ART outcomes. No missing data are to be expected because of the nature of the Mobenzi data collection tool. To monitor the attrition between the first and second wave, an attrition analysis will be conducted.

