### Monitoring

When baseline data become available, descriptive analysis and structural equation modelling using Mplus will be conducted. A special data monitoring committee, made up of delegates from both institutions and external institutes, will be informed on the progress of the trial. This committee is independent from the sponsor and funders. Furthermore, the study will be guided by a steering committee, consisting of the two local principal investigators and a postdoctoral fellow.

A debriefing and internal monitoring plan will be followed to further monitor the intervention progress and to assess quality of delivery. Adverse events resulting from the intervention are reported on the same day to the principal investigator who will report these to the ethics committee of both institutions involved in the study (the University of the Western Cape and the University of Antwerp). However, no extreme adverse events are anticipated. In case psychological support is needed, the research team will provide counselling contacts.

One key to monitoring and evaluation is establishing whether it is ethical to continue the trial. To limit the potential risks for participants, we will organise a mid-term review of the intervention to assess its initial impact. In the unlikely event that the intervention has a negative impact on the health or mental well-being of the participants the trial will be stopped immediately. The project partners (the University of the Western Cape and the University of Antwerp) must mutually decide this in consultation with one another and the ethics committees of both institutions.

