### Ancillary and post-trial care

There are essentially three groups of participants: 1) HIV patients on ART; 2) household members; and 3) CHWs providing the intervention. Groups 2 and 3 are not exposed to any risks. These participants will share their views and experiences regarding life in the household (group 2) and their work (group 3), respectively.

The PLWH enrolled in the cluster-RCT (group 1) are exposed to two potential risks for which we have developed strategies to prevent and mitigate possible negative effects. First, the patients on ART receiving the standard treatment (CHW support) are not exposed to any potential negative effect. The Non-Governmental Organisation (NGO) providing the CHW support has been providing this support for several years and is accredited and funded by the provincial Department of Health. These trained CHWs have a standard procedure to protect the person living with HIV from any unintended consequences (e.g. the disclosure of their HIV status to the family/community). Patients starting treatment follow counselling sessions at the clinic where they are introduced to their CHW, who then makes an appointment for follow-up support visits (starting with a home assessment to record the social and housing conditions). If the patient does not want the CHW to visit their home, the meetings with the CHW are organised at their preferred location. This standardised procedure has been working for many years and has assisted thousands of HIV patients to commence their treatment. No unintended consequences are therefore expected in this arm. The HIV patients in the intervention arm, however, will be subjected to a household intervention. The intervention is based on the available literature on intervention development and the theoretical frameworks developed in family sociology and psychology [39]. The entire development process also incorporated all relevant stakeholders, namely HIV patients, CHWs, the Department of Health and the City of Cape Town. However, it must be noted that every intervention can have unintended (negative) consequences. When the CHW or fieldworkers deem necessary, they will also provide contact details for relevant referrals to health or social development government services or community-based or NGOs experienced in mitigating negative family dynamics and HIV treatment difficulties.

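### The rule for participants who have an adverse event does not separate stopping intervention visits from stopping outcome collection, so read literally it allows discretionary, health-related loss of the adherence outcome after allocation

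*Protocol article*

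**What the plan says.** Two adjacent sentences in *Implementation of the HIV competent household intervention* govern participants who stop early. On a participant's own wish: "If an individual participant does not want to continue participating in the study the intervention for this particular respondent will be stopped". On an adverse event, with hospital admission as the example: "the principal investigator will make an informed decision whether or not to continue the trial for this particular participant". The first sentence pairs leaving the study with stopping the intervention. The second takes the trial itself as the thing that may stop.

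Other sections bear on this:

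- *Trial design*: "Further blinding of the study arms was not possible because of the clear differences between the intervention and the standard of care". No separate blinding of the principal investigator is described.
- *Monitoring*: "Adverse events resulting from the intervention are reported on the same day to the principal investigator", for onward report to the ethics committees.
- *Ancillary and post-trial care*, on the control arm: "No unintended consequences are therefore expected in this arm".
- *Outcomes*: "Data on ART adherence is collected from the enrolled individual by the research team". Viral load comes from data that the Department of Health already collects.
- *Follow-up data collection*: "If a patient drops out, the research team will try to trace the patient to understand the reason for this loss to follow-up".
- *Quantitative data analysis*: "First, we will perform an intent-to-treat analysis". A dose-response analysis follows. No missing data are expected, because of the data collection tool, and an attrition analysis is planned.

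**The concern.** Stopping visits and stopping measurement are different acts. The first is a matter of care and delivery. The second decides who contributes to the comparison. As worded, the adverse-event sentence can be applied as either, by someone who may know the arm, after allocation, and in response to an event that reflects the participant's health.

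Participants have started or restarted ART within four weeks of enrolment. A hospital admission in this group could plausibly go with poor adherence. If the trial ends for such a person, the postintervention adherence questionnaire is not administered, and the tracing step asks only why the person left. An intent-to-treat analysis keeps people in their allocated arm, but it cannot recover an outcome that nobody collected. A tool that prevents skipped items does not supply a survey that never took place.

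Adherence is a primary outcome and the one on which the sample size rests. If loss is selective and unequal between arms, the adherence difference shifts without any effect of the intervention.

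**Working it through.** **1. The plan's own figure.** Inputs from *Sampling*: 68% against 83%, 90% power, two-sided 5% unpooled Z test, intracluster correlation 0.0020, six clusters per arm, hence 180/6 = 30 per cluster.

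- Individual-level n = (1.960 + 1.282)² × (0.68×0.32 + 0.83×0.17) / 0.15² = 167.5 per arm.
- Design effect = 1 + (30 − 1) × 0.0020 = 1.058.
- 167.5 × 1.058 = 177.2, which becomes 180 as six clusters of 30. Power at 180 is 0.904.

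The stated 180 per arm reproduces. This point does not change it.

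**2. Which outcome is exposed.** Adherence needs contact by the research team, so it is lost if the trial ends for a participant. Viral load sits in routine records and can still be extracted. No section says that extraction stops.

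**3. What a loss could do.** The document gives no removal rate and no adherence rate among those removed, so both are assumed. Suppose there is no true effect, with p = 0.68 adherent in both arms. A share f of the intervention arm only loses its outcome, and a proportion q of these people would have been adherent. Then:

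observed rate = (p − f·q)/(1 − f), and spurious gain = f·(p − q)/(1 − f).

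With q = 0.30:

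- f = 5%: (0.68 − 0.05×0.30)/0.95 = 0.700, a gain of 2.0 points.
- f = 10%: (0.68 − 0.10×0.30)/0.90 = 0.722, a gain of 4.2 points.

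The range of spurious gain, in percentage points:

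| Adherent among those removed (q) | f = 2% | f = 5% | f = 10% |
|---|---|---|---|
| 0% | 1.4 | 3.6 | 7.6 |
| 30% | 0.8 | 2.0 | 4.2 |
| 34% | 0.7 | 1.8 | 3.8 |
| 68% (same as the rest) | 0 | 0 | 0 |

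**4. Effect on the test.** Let SE² = [p(1−p)/n + p′(1−p′)/(n(1−f))] × [1 + (n/6 − 1) × 0.0020], where p′ is the observed rate above. The chance of a significant result with no true effect, nominally 5%, is:

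| q | n per arm | f = 2% | f = 5% | f = 10% |
|---|---|---|---|---|
| 0% | 180 | 5.9% | 11.0% | 32.9% |
| 0% | 320 | 6.5% | 15.3% | 50.7% |
| 30% | 180 | 5.3% | 6.8% | 13.2% |
| 30% | 320 | 5.5% | 8.1% | 19.1% |
| 34% | 180 | 5.2% | 6.4% | 11.5% |
| 34% | 320 | 5.4% | 7.5% | 16.2% |

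**5. Dependence on one-arm removal.** If the same share of similar patients is lost from both arms, both rates move together and the spurious difference is zero. If 10% are lost from the intervention arm and 5% from control, with q = 0.30 in each, the difference is 72.2 − 70.0 = 2.2 points, about half the one-arm figure.

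**The case against.** The strongest reply is that the sentence stands under a heading about implementing the intervention, and that the sentence before it uses study and intervention almost interchangeably. Ending the trial for someone may mean no more than ending the visits. That reading is possible. What the text establishes is an ambiguous rule, not a settled policy of excluding people from the whole trial. The ambiguity still matters, because staff who follow the words can stop data collection.

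A reader might infer three stronger points, which the document does not support:

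- **That the rule removes intervention patients more readily.** The adverse-event sentence names no arm, and its example is any admission. CHWs visit both arms, so admissions can be noticed in both. *Monitoring* sets same-day reporting for intervention-related events. It does not say that other events never reach the principal investigator, and it does not define the trigger. Because that is the only stated reporting route and no unintended consequences are expected in the control arm, imbalance is plausible, but it is an inference.
- **That viral suppression figures would be inflated too.** Viral load comes from routine records and is largely protected.
- **That the rule contradicts the intent-to-treat analysis.** Nothing says that these participants are dropped from analysis or reassigned. Follow-up is meant to cover the same respondents in both arms, and tracing for the reason does not forbid an outcome survey. The supportable statement is that the comparison could be incomplete.

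It is also fair to say that the article condenses a fuller protocol and that no extreme adverse events are anticipated. The first does not settle the point, which rests on a rule the article states. The second suggests that the removal share may be small.

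**Conclusion.** The point holds as a defect of wording with a possible consequence for bias. The article gives the principal investigator, for whom no blinding is described, a decision over continuing the trial for a participant after an adverse event, and does not separate visits from outcome collection. Read literally, this allows selective loss of questionnaire adherence after allocation, which the intent-to-treat label would not repair.

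The size is unknown. Under one-arm removal of 5 to 10% with 30% adherent among those removed, the spurious gain is 2.0 to 4.2 points against a planned difference of 15. At 2% removal it is below 1 point. It is zero if those removed are as adherent as the rest or if removal is alike in both arms. All removal shares and adherence rates among those removed are assumptions. The document does not show that any such bias will occur, or that it would favour the intervention arm. The change is worth making because it is cheap and closes the route whichever reading was meant.

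**What to change.** In *Implementation of the HIV competent household intervention*, reword the adverse-event sentence so that the principal investigator's decision concerns the intervention visits only. Leave unchanged when and why visits stop. State that a participant whose visits stop remains in the allocated arm, is offered the postintervention survey, and has the Department of Health viral load extracted, unless that person withdraws from the study or from data collection. Withdrawal from the study at any time, as *Ethics, consent and permissions* allows, must stay intact. The rewording must not turn it into continued data collection without consent.

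In *Follow-up data collection*, make tracing of drop-outs seek the outcome survey as well as the reason, where consent allows.

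The cost is a wording amendment and a few extra survey attempts. Viral load access is already requested. Because recruitment began in October 2019, the amendment would reach a trial under way, and the consent terms for later record extraction should be checked first.
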